### 9.0 Risks

The risks for participants in this study due to the study procedures (interview) are anticipated to be minimal. Because our target population is AGYW who are enrolled in the DREAMS program, they are more accustomed than the average Kenyan woman to discussing sensitive topics. As an example, AGYW who are taking PrEP are asked on a quarterly basis about their risk factors for HIV infection, including questions that concern transactional sex, the number of sexual partners, gender-based violence, etc. The risks associated with participating in the current study may include the following:

Psychological risk: Participants may feel embarrassment or discomfort discussing sensitive topics such as sexual behavior, HIV services used, etc.

Social risk: There is a risk of a breach of confidentiality, which could put an individual at risk if someone were to find out sensitive and confidential information about the AGYW. For the positive controls, a breach of confidentiality could reveal her status as HIV+. Similarly, if there were a breach of confidentiality, a health care provider could be put at risk with her/her employer or community if his/her responses were viewed negatively.

In the focus group discussions, the study will ask participants not to talk with others outside the study about who was in the group or what was discussed. However, there is the risk that a participant may breach this. Also note that, by participating in an FGD, the individual is self-disclosing to other participants that they are involved in the DREAMS program, either as a participant (peer), provider, or Safe Space mentor.

Physical risks (blood sample): The participant will likely feel some pain when the staff conducts the fingerstick to take the blood sample. Other than this brief pain, the discomfort of the finger prick is minimal. This pain is comparable for tests for HIV infection, which are conducted on a quarterly basis with all PrEP participants. In about one out of 10 cases, people have a small amount of bleeding under the skin or a bruise. For some people they may have a small scar for a few weeks. The risk for localized infection from the fingerstick is less than 1 in 1,000.

### 10.0 Mitigation of risks

Efforts will be made by study staff to mitigate risks of study participation described above as follows:

A private setting will be used for the all participant interviews. All participants (AGYW, peer, mentor and health care providers) will be informed that they do not have to answer any question they do not wish to answer, and that they are free to withdraw from the study at any time. Interviewers will be trained to remind participants of this during the interview if a participant is visibly embarrassed or uncomfortable by a question.

For the positive controls (who are HIV+), all interactions with potential participants will be conducted in a private setting to minimize the risk of any breach of confidentiality. In addition, participants will be given the option to decline to take a copy of the ICF so as to reduce possible exposure of her HIV+ status at a later time.

In the focus group discussions, the study will ask participants not to talk with others outside the study about who was in the group or what was discussed. Participants will also be asked to not use names during the discussions e.g., when talking about young women or referencing each other. The study will redact names in the transcripts that may be inadvertently mentioned during the discussions.

To lessen risks of bruising and infection from the fingerstick blood sample, the study will employ experienced HTS workers as study staff to take the blood samples. These staff are experienced with handling blood products, and will have additional training to take the blood samples, consistent with sampling and testing requirements for Tenofovir.

AGYW participants who do not want to have their blood sampled for TDV/FTC testing will be counseled that choosing not to have their blood sampled and/or not participating in the interview will not affect their participation in the DREAMS program or their enrollment on PrEP.

All efforts will be made to maintain confidentiality and data security. Study staff will participate in training for study confidentiality, including conducting interviews and focus groups in private settings, securing data on password protected devices, keeping paper forms and tape recordings in locked cabinets/rooms, and maintaining all information collected by the study as confidential, not to be shared with individuals who are not part of the research team. Consent witness will also be trained regarding ethics of research consent, with particular emphasis on protecting the confidentiality and privacy of participants.

### 11.0 Benefits

Participants of the study will receive no direct benefit. However, DREAMS participants, including those who participate in the study, may benefit in terms of improvements in the way PATH implements the DREAMS program and the provision of PrEP services, based on the insights they provide.

We expect the societal benefits of the study may be to women and girls, and their communities in Kenya and potentially beyond by furthering knowledge about how to increase adherence to PrEP for this population and hence decrease the HIV burden. Input from DREAMS program participants – AGYW, mentors and providers – may help to improve the services received through DREAMS.

### 12.0 Study and safety monitoring

Study staff will make routine, biweekly visits to the field during data collection to meet with interviewers and discuss study implementation, with a focus on the informed consent process, preservation of confidentiality, data management and security, challenges with contacting participants or other recruitment issues, challenges with data collection, etc.

In addition, to ensure that study staff are implementing the study according to the protocol, an audit will be conducted in which a sample of participants who have been interviewed to date are contacted to confirm their involvement, and ensure that informed consent procedures were followed. Participants will be selected at random, and interviewers will not know in advance which participants will be contacted.

### 13.0 Managing and reporting adverse events

An adverse event (AE) is any untoward or undesirable event experienced by a participant regardless of whether the event is expected or related to the participant’s involvement in the research. Given the nature of the study intervention (an interview and DBS), we do not anticipate any serious adverse events in this study aside from the risks described in previous sections. See also the next section.

### 14.0 Managing and reporting unanticipated problems or protocol deviations

In this study, an unanticipated problem is any incident, experience or outcome (physical, psychological, economic or social) that potentially places the participants or others at greater risk for harm.

Participants will be provided with contact information for staff (in the informed consent) and reminded that they should contact the staff in the event of any unanticipated problems arising from their experience as a study participant.

Staff are required to report any unanticipated problems or deviations to protocol that occur during the study to the Study PI within 24 hours of learning about issue. Within 72 hours, the Study PI will notify involved appropriate Ethics Committees in accordance with their reporting requirements.

### 15.0 Confidentiality and data management

All study staff will participate in training for study confidentiality as follows: Study staff will maintain all information collected by the study as confidential. Only study staff will have access to data, tape recordings, and personal information that identifies study participants. Only study investigators will have passwords to access computers and keys for files where study data (including tape recordings) are stored. Only study identification numbers will be used to label study records, tape recordings, and transcripts. Any identifying information will be deleted/redacted from transcripts.

We will store the tape recordings until they are transcribed into computer records. We will erase tape recordings as soon as possible after they are no longer needed.

We will only label blood samples with a study identification number and no other identifying information. We will store samples securely and only allow relevant study staff to access samples. Samples will be stored for up to five years after study activities have been completed and then be destroyed. Samples will only be used for this study to test for PrEP medication levels. The samples will not be tested for HIV or any other tests in this or any future studies. Linking documents connecting the participant’s name and other identifying information to the study identification number will be maintained for quality control (auditing) and any necessary follow-up (missing data, etc.). Linking documents and other personal information will be destroyed as soon as possible within five years after study activities have been completed e.g., after all study data has been verified and cleaned and/or necessary follow-up has been conducted.

Study reports and presentations will not contain any personal identifying information of any study participant.

Trained study staff will collect semi-structured data from study participants electronically using mobile phones or tablets, using Open Data Kit or similar data collection software. Data will be uploaded to a server immediately post-interview or as soon as connectivity can be established if the network is poor. Phones and/or tablets will be password protected and personal identifying data will not be entered. Paper questionnaires may be used in the event of technological challenges and/or poor connectivity. These documents will only be labeled with the study identification number.

The in-depth interviews will be audio recorded. ID numbers will be used to identify participants and names will not be collected on the audio recording. Similarly, the recordings will be transcribed to password protected computers, and the transcripts will contain only the study ID number.

Data collected in the study will not be disclosed to any health officials, will not be entered into the medical record of the participant, nor reported to health center.

In accordance with funder’s requirements, de-identified data will be made available in a data repository. Study records will be retained for 5 years after the end of the study and then destroyed.

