**Figure 2: Sample of AGYW study participants**

**Sample at Time 1** **Sample at Time 2**

Longitudinal sample

Longitudinal sample

We will supplement and enhance our understanding of factors critical to PrEP adherence through qualitative data collection. Specifically, we will conduct two focus groups with AGYWs who are 18+ years old (AGYW peers) but not enrolled on PrEP, two focus groups with DREAMS health care providers and two focus groups with DREAMS mentors who coordinate the DREAMS Safe Space activities. The AGYW peer focus groups are intended to explore the influence of peers on AGYWs’ PrEP enrolment and adherence. We target AGYW who are not themselves enrolled on PrEP in order to better understand the social climate in the communities where our participants reside. Understanding the social environment is critical for studies involving AGYW because of the strong influence these social spheres have over AGYW’s health and behavior.^[[46]](#endnote-46)^ Focus group participants will be drawn from the same wards as the AGYW who participate in interviews and biomarker sampling.

Finally, we will conduct in-depth interviews (IDIs) with a subsample of 16 AGYW 18+ years who are continuing with PrEP and in-depth interviews with 16 AGYWs 18+ years who have discontinued PrEP entirely. These interviews are for the purposes of illuminating in a qualitative fashion some of the underlying behavior rationales affecting adherence as well as the underlying reasons *why* AGYWs discontinue PrEP use after enrollment. The samples of AGYW for the IDIs will be randomly drawn from among those participating in the quantitative survey (a subsample of respondents).

The outcome measure or study endpoint will be PrEP adherence as measured by the biomarker level of tenofovir. Multivariate regression analysis will determine whether differences in adherence are associated with any particular contextual co-factors. Specifically, we hypothesize that the following measures will be positively associated with PrEP adherence:

- AGYW perceived HIV risk and perceived efficacy of PrEP
- Internal and perceived HIV stigma
- Level of personal empowerment
- Perceived social support of family, friends (MODS survey)
- Trust, confidence in provider and mentor
- Level and nature of involvement in DREAMS activities
- Regularity of PrEP provision at Safe Spaces
- Receptivity of provider to AGYW use of PrEP
- Community support for DREAMS, PrEP
- Lower depression scores (PHQ-9)

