- Lower alcohol use (AUDIT)
- Lower intimate partner violence (PVS/HITS)
- Higher food security (USDA/WHO)

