**Sample size**

The sample size of AGYW who will participate in the interviews and provide biomarker samples at Time 1 is 350. Interviews will be repeated after 3 to 4 months for all participants, and biomarkers collected again for those who continue in the PrEP program. Assuming a continuation rate of 40% (and 10% loss to follow up), we expect to collect 175 repeated DBS samples, for a total of 525 samples.

PrEP Adherence at each time point will be primarily measured by the percentage of AGYW whose PrEP drug levels in dried blood spots reached a certain threshold reflecting the exposure to PrEP drug in the recent past. Specifically, PrEP adherence will be measured by the percentage of AGYW whose tenofovir-diphosphate drug levels in DBS exceeds 30f/molx106, which is consistent with an average of at least four PrEP doses per week.

Assuming a discontinuation/ loss to follow-up rate of 50%, and a two-level factor (potentially associated with PrEP adherence), this sample size will allow us to detect cross-sectionally at the first time point a minimum absolute difference of 15% in the PrEP adherence rates between the levels of the factor at 80% power given a type I error rate of 5% and a two-sided test (Table 3).

**Table 3.** Sample size and power considerations for AGYW interview and DBS samples

| **Absolute difference in adherence rates** | **Sample size needed to measure the absolute difference in the adherence rates** | |
| --- | --- | --- |
|  | **80% power** | **90% power** |
| 25% | 136 | 178 |
| 20% | 206 | 270 |
| 15% | 350 | 462 |
| 10% | 752 | 992 |

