For the focus groups with mentors, we will randomly select potential participants from among those mentors operating in the same wards as the AGYW study participants. Study staff will contact mentors using the contact information available on record and invite them to participate in the study using a standardized recruitment script. Mentors are aware that they may be contacted for research studies and other related activities due to their participation in DREAMS, and as with any participant, may voluntarily choose to participate in the study or not.

Health care providers who are assigned to the DREAMS program Safe Spaces in the same wards as the AGYW study participants, and who have received training in PrEP will be randomly selected and recruited. These providers have responsibility for providing routine PrEP refills and assessments for DREAMS participants at the Safe Space. A study staff will approach health care providers during these visits or at their place of work to ask if they are willing to participate in the study following an approved recruitment script.

*Recruitment for in-depth interviews*

Participants who meet the additional eligibility criteria for either type of IDI (continuing PrEP or discontinuing PrEP) will be randomly selected from among those participating in the second interviews. In-depth interviews will be audio-recorded, conducted at a place of convenience to the respondent, and lasting no more than one hour.

*Recruitment of positive controls*

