The Afya Ziwani team collects data on HIV+ AGYW who participate in their program. Based on their program records, the Afya Ziwani team will identify a convenience sample of potential positive controls who meet the eligibility criteria (female 18+ years old, living in Kisumu or Nyamira county, taking tenofovir for ART, virally suppressed as per testing within the past month, and penultimate viral load test demonstrating suppression). An Afya Ziwani staff person will contact the individual about their willingness to be contacted about future studies via phone or at the Safe Space. S/he will introduce the study and their specific role in the study using an approved recruitment script. The role of the Afya Ziwani project staff (who are not research staff) ends with identification and preliminary recruitment of potential participants whose medical records suggest they fit the eligibility criteria. Once a potential participant agrees to meet with a PATH research staff person, all study procedures are conducted by study staff, including informed consent, verification of eligibility and DBS sampling.

For those who are interested, an appointment will be made to assess eligibility and conduct the informed consent. Note that the consent form includes release of the patient information relevant for eligibility assessment (type of ART, viral load at most recent test, date of most recent test, viral load at penultimate test); study staff will be blinded to this patient information unless the participant consents to share it. For individuals who are eligible and consent to participate, a DBS will be collected. Once the DBS is collected, their participation in the study ends.

Recruitment and participant engagement procedures will be adapted to the COVID context. Specifically, the procedures outlined below will be followed to ensure the safety of participants and research staff:

- We will comply with country and county public health authorities and government requirements. Through Afya Ziwani, the study team will meet with members of sub-County and County Health Management to discuss study plans including plans to adhere to all COVID-19 protocols.
- We will ensure that water and soap for handwashing and/or hand sanitizers are available in all locations where individuals will meet the study team. In addition, we will provide participants in this study with a face mask.

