### 7.0 Illustrative lines of inquiry

**AGYW participant**:

| **Topic** | **1^st^ interview** | **2^nd^ interview** |
| --- | --- | --- |
| Principal rationale or motivation for participating in the DREAMS program | X |  |
| Principal rationale or motivation for initiating PrEP | X |  |
| Experience of care, receiving PrEP via Safe Spaces | X |  |
| Self-reported adherence to PrEP regimen | X | X |
| Perceived challenges with PrEP adherence | X | X |
| Reasons for discontinuing PrEP |  | X |
| Level of social support (including partner, family and community) for PrEP | X | X |
| Current level of HIV risk and perception of HIV risk | X | X |
| Perceived HIV stigma | X | X |
| Perceived efficacy of PrEP | X | X |
| Degree of self-efficacy/personal empowerment | X |  |
| Indicators for depression/mental health | X | X |
| Alcohol use | X | X |
| Experience of violence | X | X |
| Food security | X | X |

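### The confidentiality rules in Sections 10.0 and 15.0 carry no exception for the participant's agreement or imminent danger, although both interviews ask about depression and partner violence

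*Protocol*

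**What the plan says.** **What is asked.** The AGYW participant table in Protocol Section 7.0 schedules "Indicators for depression/mental health" at both the first and second interview, and does the same for experience of violence. The hypotheses under Study design in Section 3.0 name the instruments: PHQ-9 for depression and PVS/HITS for intimate partner violence. The Data analysis text lists both as co-factors for adherence.

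**What staff may do with the answers.** Section 10.0 describes confidentiality training that includes "maintaining all information collected by the study as confidential, not to be shared with individuals who are not part of the research team". Section 15.0 states "Data collected in the study will not be disclosed to any health officials, will not be entered into the medical record of the participant", and the same sentence excludes reporting to the health center. Earlier in Section 15.0, staff are told in general terms to keep all study information confidential.

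**What happens when something is wrong.** Section 14.0 requires staff to report an unanticipated problem to the principal investigator within 24 hours. The principal investigator then informs the ethics committees within 72 hours. Section 13.0 foresees no serious adverse events beyond the risks already described, and Section 17.0 foresees no injuries.

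**The concern.** An interviewer using a depression scale and a partner-violence screen can expect some answers that call for help. The natural person to tell is the provider at the woman's Safe Space. Section 6.0 says of these providers: "These providers have responsibility for providing routine PrEP refills and assessments for DREAMS participants at the Safe Space".

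The two confidentiality sentences are written without conditions. A trained interviewer who follows them to the letter could not pass on a disclosure of self-harm risk or of a violent partner, even if the woman agreed to it. At stake is participant safety, and also the position of staff, who would have to choose between the written rule and what they judge right. The estimates of adherence are not affected.

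**Working it through.** No arithmetic applies. The check sets the relevant sections side by side.

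1. **Are the topics asked of everyone, twice?** Yes. Section 7.0 marks depression and violence for both interviews. The table row says only violence; that it concerns partners follows from the PVS/HITS entry in Section 3.0 and from the Data analysis text.

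2. **Is a Safe Space provider outside the research team?** Yes. Section 8.0 requires a consent witness to be outside the research team and gives a Safe Space mentor or health care provider as suitable examples. The sharing rule in Section 10.0 therefore covers these providers.

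3. **Does Section 15.0 cover them too?** Not plainly. It names health officials, the medical record and the health center. Sections 1.0 and 7.0 contrast community venues such as Safe Spaces with health facilities. The explicit bar on telling a Safe Space provider rests on Section 10.0. Section 15.0 separately closes the formal health-system routes.

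4. **Is there an exception for agreement?** None is written for information leaving the study. The protocol does write such a clause where it wants one. For the positive controls, Section 6.0 says "study staff will be blinded to this patient information unless the participant consents to share it". That clause governs records coming into the study from the Afya Ziwani programme, which is the opposite direction.

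5. **Is there an exception for danger?** None in Sections 10.0, 13.0, 14.0, 15.0 or 17.0. Section 10.0 meets distress during an interview with privacy, the right to skip a question and the right to withdraw. Section 14.0 defines an unanticipated problem broadly enough to include psychological and social events that raise the risk of harm, but its route ends at the ethics committees and names no step to care.

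6. **What does the programme already provide?** Section 1.0 lists interventions against gender-based violence within DREAMS and a form that records services received at the Safe Space or by referral. Section 9.0 says that women taking PrEP are asked every quarter about risk factors, including gender-based violence. For a woman on PrEP, the programme can therefore learn of violence without the study. No comparable DREAMS question on depression appears in the text shown. A woman who has discontinued is, by the definition in Section 4.0, at least 60 days overdue for a refill and reports that she is not taking PrEP. She still has the second interview. The quarterly route is weaker for her, although Section 6.0 describes Safe Space attendance at least monthly for DREAMS activities in general, so she may still be seen.

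**The case against.** The strongest reply is that these sentences protect young women who disclose HIV risk and partner violence, and that nobody would read them as forbidding help that the woman herself requests. The protocol does not treat its own rule as absolute: the ethics committees of Section 14.0 are not part of the research team, and Section 15.0 sends de-identified data to a repository. The consent forms, the SOPs and Section 19.0 are not available here and may set out limits to confidentiality or a referral procedure.

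Much of this stands. A reader might infer that the study has no referral procedure. The documents do not support that, because the places where one would normally sit are not shown. A reader might also infer that women in danger are left without any help. That goes too far: staff may advise a woman to seek care, they must escalate an unanticipated problem to the principal investigator, and DREAMS has its own violence services.

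The wording itself remains open to objection. The two outward flows that the protocol allows are to oversight bodies and of de-identified data; neither is a route to care. A procedure elsewhere that passed identifiable information to a provider would conflict with Section 10.0 as written. An agreement clause is easy to write, as Section 6.0 shows.

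**Conclusion.** The point holds as a defect of wording with a bearing on participant safety. It is a cheap improvement, minor to moderate in weight. Followed literally, Section 10.0 stops staff from telling a DREAMS provider what a woman has disclosed, even with her agreement, and Section 15.0 stops them from telling the health system. The gap is partly filled for violence among women still on PrEP, less so for women who have stopped, and not at all for depression in the text shown.

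This rests on reading the two sentences as they stand and on no exception appearing in the parts of the protocol available. If the consent form or SOPs state one, the remaining task is to make the protocol agree with them.

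A reader might try to size the problem from the Sample size text, which says "Assuming a continuation rate of 40% (and 10% loss to follow up), we expect to collect 175 repeated DBS samples". With 350 women and 10% lost, 350 × 0.90 = 315 would be interviewed again, and 315 − 175 = 140 would have no second sample. These figures count interviews and expected discontinuers, not women at risk. Treating the 140 as discontinuers also means reading the stated 40% as a discontinuation rate, since 350 × 0.40 = 140 does not give 175 samples. The protocol gives no prevalence of severe depression or imminent danger, so no count of affected women is supported.

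**What to change.** Add one clause to the sharing rule in Section 10.0 and to the disclosure sentence in Section 15.0: *except with the participant's agreement, or as the ethics committees require where there is imminent danger*. Align the consent text so that women know the limit before they answer. If the consent form or SOPs already hold a referral procedure, cross-reference it from Section 10.0.

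A same-day referral step to an existing DREAMS provider, with a responsible study role, would be a useful option but is not needed to cure the wording. The sponsor and its clinical advisers should decide what triggers any referral.

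The cost is a wording change in two sections and the consent text, with a short addition to the confidentiality training already planned. The downside is that a stated limit to confidentiality may slightly reduce disclosure of depression or violence.
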